#### Secondary outcomes

The secondary outcome measures will include improvement in motor function indices and quality of life measures, i.e., modified Ashworth scale (MAS) [33, 34], Motricity Index [35], Rankin Scale (RS) [36], modified Barthel Index (mBI) [37]. These tests will be administered at both T0 and T1. A further assessment will be performed 6 months (T2) after the end of the treatment to evaluate the retention of the effect.

#### Functional MRI study

A subgroup of participants (approximately 20 individuals equally distributed in the two groups, i.e., 10 for experimental and 10 for control group) will be involved in a functional MRI (fMRI) study, to assess plastic changes in the MNS activity following the application of the rehabilitation treatments. fMRI will be performed in two sessions, one before (T0) and one after the end of the treatment (T1) within 72 h. Before starting each functional imaging session, participants will undergo a training session lasting 15 min, in order to allow them to familiarize with the MR system and the experimental procedure. After, patients will be invited to participate in the real fMRI session (divided into 4 short runs lasting approximately 7 min each).

The patient will be instructed to perform two experimental tasks: a) *action observation* (functional runs 1–2); b) *motor task* (functional runs 3–4).

#### Action observation

During the first two functional runs, visual stimuli will be presented in binocular vision by means of Liquid Cristal Display (LCD) goggles (VisuaStim-SVGA-Resonance Technology, USA). Participants will observe short video-clips (lasting 4 s each), showing unimanual or bimanual actions performed by an actor, from a subjective perspective. The observed actions will consist in grasping and using different tools (e.g., hammering, using a screwdriver, opening a jar etc.), or as control condition, observation of the static initial frame of each clip. The objects will be of different colors in order to increase the visual variability of the stimuli. The visual characteristics of each video will be balanced between the experimental conditions to control the effects of brightness, contrast, sharpness and the amount of visual information. A total of 72 video clips will be created (9 objects × 4 colors × 2 conditions).

Each experimental and control condition will be presented 72 times during the experiment, 36 times for each session. The videos will be presented in independent blocks (*N* = 12) for each condition and each block will contain 6 videos, interspersed with an inter-stimulus period of 800 ms. The duration of each block will be 28 s. A number of 12 blocks will be acquired in each observation run, 6 per condition, followed by a variable *rest* period, lasting 16-20 s. During the *rest* period, in the absence of experimental stimuli, the patients will have to fixate a white cross on a black background.

#### Motor task

In the functional runs 3 and 4, participants will be instructed to perform a motor task consisting in tool manipulation performed with the paretic hand or with both hands. The task will be arranged as for the previous sessions using a block design (block duration: 26 s), in which each block will include 3 motor trials, interspersed with *rest* periods (duration: 16-20 s). During *rest* the patient will simply remain still, fixating the experimental setting, i.e., the own hands and the tool mounted on the apparatus. As control conditions, in separate blocks, participants will perform a simple motor task, consisting in reaching a tool without manipulating it (3 trials per block). Each motor trial of the experimental and control conditions will be presented 30 times for each run (10 blocks per run for each condition). Thus, the entire motor session will consist of 40 blocks, divided in 20 tool manipulation blocks and 20 control reaching blocks.

#### MRI data acquisition and statistical analysis

Structural and functional images will be acquired using a 3 T General Electric scanner (MR750 Discovery) equipped with a 32-channel receiver head-coil. Functional volumes will be acquired either while participants perform the action observation task and the motor task with the following parameters: forty axial slices of functional images covering the whole-brain acquired using a gradient-echo echo-planar imaging (EPI) pulse sequence. Its acquisition parameters will be: slice thickness = 3 mm plus interslice gap = 0.5 mm, 64 × 64 × 37 matrix with a spatial resolution of 3.5 × 3.5 × 3.5 mm, repetition time (TR) = 2000 ms, echo time (TE) = 30 ms, field of view (FOV) = 205 × 205 mm^2^, flip angle = 90°, in plane resolution = 3.2 × 3.2 mm^2^. A three-dimensional (3D) high-resolution isotropic T1-weighted IR-prepared Fast SPGR sequence (called BRAVO, BRAin VOlume) will be acquired as anatomical reference. Its acquisition parameters will be set as follows: 196 slices, 280 × 280 matrix with a spatial resolution of 1 × 1 × 1 mm, TR = 9700 ms, TE = 4 ms, FOV = 252 × 252 mm; flip angle = 9°. The protocol will comprehend a 3D fast spin-echo (FSE) fluid attenuated inversion recovery (FLAIR) sequence (called CUBE FLAIR). The 3D FLAIR is based on 3D-FSE extended echo train acquisition, an advancement of 3D-FSE extended echo train acquisition, an advancement of 3D-FSE in which refocusing flip angle modulation and 2-dimensional acceleration enables volumetric coverage with high in- and through-plane resolution with reduced RF power deposition. Its acquisition parameters will be set as follows: 196 slices, 280 × 280 matrix with a spatial resolution of 1 × 1 × 1 mm, TR = 7000 ms, TE = 118 ms, Echo Train Length 200 ms; FOV = 256 × 256 mm; matrix size 256/256 mm; acceleration factor 2/2. A Diffusion Tensor Imaging (DTI) sequence will be also included: diffusion gradients (b value = 1000 s/mm^2^) applied in 64 noncollinear directions, 8 measures without diffusion gradients (b = 0 s/mm^2^), 45 axial slices with 3 mm slice thickness, FOV 240 × 296 mm, matrix size 80 × 80 (in-plane resolution, 3.0–3.7), TR = 11,000 ms, TE = 92 ms.

#### Sample size

According to CONSORT guidelines [38, 39], the estimated sample size is based on projected treatment effects on the primary outcome measure, the BBT. Based on the available literature [32], we consider a 7-point change in BBT scores at post-test (T1) as a clinically significant effect. Based on a common standard deviation at post-test equal at 11.3 and a drop-out rate of 10%, we estimate that a sample of 47 subjects for each group (*N* = 94) will have a statistical power of 80% to detect a significant difference between the two measurements.

Concerning the fMRI study, the sample size estimate is based on the calculation of the level of change in the Blood Oxygenation Level Dependent (BOLD) signal detected in a previous fMRI study with an action observation paradigm (number of subjects per group = 10). Significant activation clusters within the MNS, including the PMv and the IPL, were considered for the analysis, using a statistical threshold of *p* < 0.001 with Family Wise Error (FWE) correction for multiple comparisons at the cluster level. The Power Analysis (software: NeuroPower-tool) conducted on this study showed that to obtain a change in the BOLD signal with a significance threshold of *p* < 0.05 and a minimum statistical power of 80% with Bonferroni correction, it is necessary to recruit at least 9 participants per group. However, regardless of the presence or absence of effects at the group level, patients will also be treated as a case-series, so that assessment of BOLD change following treatment will also be performed at the single case level.

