#### fMRI statistical analysis

All functional volumes will be preprocessed and analyzed using SPM12 software (http://www.fil.ion.ucl.ac.uk/spm), implementing a standard pipeline which includes spatial realignment, slice-timing correction, anatomo-functional coregistration, normalization to the Montreal Neurological Institute (MNI) template and smoothing. At group level, significant brain activations will be assessed using the General Linear Model (GLM). Parametric maps (*t* contrast) of the activation will be calculated in the whole brain for each experimental and control condition. Subsequently, to assess possible differences between subjects, a ROI (Regions of Interest) analysis will be performed in the main MNS areas, extracting the BOLD signal associated with each condition. Student’s t-test will be used to evaluate the significance of BOLD signal differences between conditions. All parametric statistical maps will be corrected for multiple comparisons by applying the Family Wise Error (FWE) method, with a significance level set at *p* < 0.001. In addition to the univariate statistical analysis, advanced analyses including Psychophysiological Interaction and Dynamic Causal Modeling will be performed in order to measure effective functional connectivity changes between MNS areas, following the application of the rehabilitation treatment.

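### The fMRI sub-study's 80% power at 9 per group is stated for a corrected p < 0.05, but the maps are to be judged at FWE p < 0.001, so as written the figure does not apply to map-level inference

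*Protocol article*

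**What the plan says.** **Sample size (fMRI paragraph).** The estimate starts from "the level of change in the Blood Oxygenation Level Dependent (BOLD) signal detected in a previous fMRI study with an action observation paradigm". Clusters from that study were selected at p < 0.001 "with Family Wise Error (FWE) correction for multiple comparisons at the cluster level". The power result is then given separately, at a threshold of p < 0.05: for "a minimum statistical power of 80% with Bonferroni correction, it is necessary to recruit at least 9 participants per group".

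**Functional MRI study.** About 20 patients are planned: "10 for experimental and 10 for control group".

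**fMRI statistical analysis.** Whole-brain t-contrast maps are computed for each condition. A region-of-interest (ROI) analysis in the main mirror-neuron areas follows, using Student's t-test. The error-control rule reads: "All parametric statistical maps will be corrected for multiple comparisons", and this is done "by applying the Family Wise Error (FWE) method, with a significance level set at *p* < 0.001". No separate level is given for the ROI t-tests, and the text does not say whether the map rule works at voxel or cluster level.

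**Background.** The third hypothesis is that the experimental arm shows greater functional change in mirror-neuron activity than the control arm. The Discussion names this comparison as the specific aim of the fMRI assessment.

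**The concern.** A power figure holds only for the significance level at which it was computed. Here the sub-study is powered at one corrected level and its maps are to be declared significant at another, nominally 0.05 / 0.001 = 50 times stricter. Both levels are described as corrected for multiplicity, so this is not a corrected level being confused with an uncorrected one. The 0.001 in the sample-size paragraph does not bridge the gap, because it describes how clusters were picked from the earlier study and not the level of the power result.

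Two things are at stake for hypothesis 3. A null group map could be read as evidence from a study with 80% power when the written criterion gives less. And with two levels on the page, the threshold could be chosen after the maps have been seen.

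**Working it through.** **Inputs from the article.** Powered level 0.05, Bonferroni-corrected. Power at least 80% at 9 per group. Map level 0.001, FWE-corrected. Planned enrolment about 10 per group. Effect size, SD, number of tests and sidedness are not given.

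**Reproducing the plan's figure.** Not possible without those inputs. The check therefore back-solves the effect that the 80% implies and re-tests it at the stricter level.

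**Assumptions.** The same number of comparisons m applies at both levels, with m = 1 to 50,000. The test is a single t-test, two-group or paired, two-sided unless stated. Power at 9 per group under 0.05/m is exactly 80%.

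**Formulas.**
- Two-group: df = 2n − 2, noncentrality d·√(n/2).
- Paired: df = n − 1, noncentrality d·√n.
- Power = P(noncentral t > t critical at α/2).

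**Worked case by normal approximation (two-group, m = 1).**
- d = (1.960 + 0.842) / √(9/2) = 2.802 / 2.121 = 1.321.
- At α = 0.001 the critical value is 3.291.
- n = 9: Φ(2.802 − 3.291) = Φ(−0.489) = 31%.
- n = 10: 1.321 × √5 = 2.953; Φ(2.953 − 3.291) = Φ(−0.338) = 37%.

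**Same case by noncentral t.** d = 1.41. With 16 degrees of freedom the critical value rises from 2.120 to 4.015. Power falls from 80% to 21% at n = 9 and is 27% at n = 10.

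**Over the range of m, at level 0.001/m:**

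| Test | 9 per group | 10 per group | n per group for 80% |
|---|---|---|---|
| Two-group t, two-sided | 21–29% | 27–52% | 21 down to 12 |
| Paired t, two-sided | 14–16% | 20–40% | 21 down to 12 |
| Two-group, normal approximation | 31–55% | 37–67% | 20 down to 12 |

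At 10 per group the higher powers go with larger m. One-sided t-tests give 14–29% at n = 9 and 18–51% at n = 10.

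**Sensitivity to the word minimum.** If 9 is the smallest whole number that reaches 80%, the effect could be somewhat larger, but it stays below the one that reaches 80% with 8 per group. At that upper limit, power at 0.001/m is 19% (paired, m = 1) to 53% (two-group, m = 50,000) with 9 per group, and 26% (paired, m = 1) to 77% (two-group, m = 50,000) with 10. The shortfall narrows at very large m but does not close within this range.

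**Direction.** For a fixed effect and sample size, a stricter level always lowers power. That part needs none of the assumptions.

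**The case against.** **The ROI tests may be what was powered.** The sample-size paragraph refers to clusters in the ventral premotor and inferior parietal areas. The ROI step covers the same kind of region and is introduced as the way to assess differences between subjects. The 0.001 rule is written for maps only. This stands. A reader might infer that the 80% belongs to a test the trial will not run, or that the sub-study will probably find nothing. The documents support neither inference: the ROI tests, the connectivity analyses and the single-case assessments (planned whatever the group result) lie outside the shortfall shown here.

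**The 0.001 may be a cluster-forming threshold.** The sample-size paragraph itself pairs 0.001 with cluster-level FWE. If 0.001 were only an uncorrected height threshold, it would not be the decision level, and the conflict would shrink or vanish: with 50 Bonferroni tests, 0.05/50 = 0.001 exactly. This is plausible, but the analysis section calls 0.001 the significance level of the FWE correction. A condensed article may omit the voxel or cluster detail, but here two levels are stated and they disagree.

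**The percentages are not the trial's own.** Correct. Bonferroni and FWE are different corrections, so a common m, and hence a 50-fold ratio per test, is an assumption. No arithmetic error in the stated 9 per group is shown.

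**Conclusion.** The point holds for the maps. As written, the 80% at 9 per group is attached to a corrected 0.05 and does not carry over to maps judged at FWE p < 0.001. The planned 10 per group does not restore it in any variant tried. The illustrative power is about 14–29% at 9 and 20–52% at 10 per group by two-sided t-test, and at most 67% by normal approximation. These figures rest on an assumed m, an assumed test type and an effect set to give exactly 80%. Allowing for rounding up to a whole patient raises the ceiling to 77% at 10 per group in the most favourable case.

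Only the direction is certain. The size depends on inputs that the article does not give, and no shortfall is shown for the ROI t-tests. Severity is moderate and confined to the mechanistic sub-study (hypothesis 3). The Box and Block Test outcome and the 94-patient sample size are untouched.

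**What to change.** Use one corrected level in the sample-size paragraph and the fMRI analysis section, by either route:

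1. Declare map-level significance at FWE-corrected p < 0.05, stating voxel or cluster level. If 0.001 was meant as the cluster-forming threshold, label it so.
2. Keep FWE p < 0.001 for the maps, rerun the power tool at that level, and replace the 80% with the power obtained at 10 per group.

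In both cases, state whether the power figure refers to the maps or to the ROI t-tests, and give the ROI tests their own level. The cost is a wording change or one rerun of the power tool, with no extra scans. The article reports that recruitment had not started at submission. If it has started since, the level should still be fixed before any group maps are examined.

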#### Recruitment

Patients considered eligible (see Methods section “Inclusion and Exclusion criteria”) will be invited from the “Cardinal Ferrari Center” and the “Clinical Institute Quarenghi” to participate in the trial, explaining them in detail the purposes and methods of the study. Before enrollment, the informed consent (see Additional file 3) will be obtained from patients, or from the caregivers.

### Assignment of intervention

#### Randomization

Participants will be randomly assigned to either control or experimental group with a 1:1 allocation using a computer-generated randomization schedule, stratified by clinical level of the hand use (minimal vs. discrete). In particular, permuted blocks of random sizes will be used. The block sizes will not be disclosed, to ensure concealment. All randomization, sequence generation, and preparation of group allocation materials will be performed by an independent researcher, who has no direct contact with the clinical aspects of the trial.

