### Participants

In general, eligible patients will be adults with a clinical diagnosis of stroke (from 3 to 18 months after the acute event, controlled via medical history and patient’s data in the respective rehabilitation center), resulting in primarily motor symptoms with unilateral upper limb paresis and residual movement ability. Only patients with severe motor symptoms or further severe neuropsychological deficits will not be eligible to participate. The multicentric study will take place in two clinical centers representing the main Italian venues for stroke rehabilitation based on VR, i.e., the “Cardinal Ferrari Center” (S. Stefano Riabilitazione) (Parma, IT) and the “Clinical Institute Quarenghi” (Bergamo, IT).

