### Interventions

#### Setting for VR rehabilitation

Each rehabilitation session will take place in a quiet room, with the patient sitting on a chair with the arms placed on a table. To provide a suitable range of movement of upper limbs, the patient’s chair will be adjusted so that the table will be at waist height (Fig. 2-A). A large monitor screen (32 inches) will be positioned 1.5 m distance in front of the patient. A trained occupational therapist (OT) or a physiotherapist (PT) will assist the participants, instructing them to pay attention to the video-clips and encouraging them during the imitation task. The Virtual Reality Rehabilitation System (VRRS, Khymeia Group, Noventa Padovana, Italy) will be used for the execution of all exercises in a VR setting. The VRRS is used as a clinical routine for the rehabilitation of a wide spectrum of diseases through the numerous rehabilitation modules containing a large library of clinically validated exercises. The system includes also a workstation connected to a 3D motion tracking system (Polhemus Liberty TM, Colchester, VT) and an integrated high-resolution monitor for the visualization of virtual scenarios.

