#### *Experimental treatment (AO* + *VR)*

Participants of the experimental group will undergo a treatment based on observation of actions followed by their immediate reproduction in VR (AO + VR treatment). The experimental treatment will consist in 18 sessions lasting about 1 h each, with a tolerance of ± 2 sessions, thus resulting in a minimum of 16 and a maximum of 20 sessions. Treatment sessions will be carried out with a frequency of about four days per week, within a period of five weeks. During the rehabilitation sessions, the patient will be instructed to carefully watch videos lasting about 1.5 min, presented on the monitor, consisting in unimanual or bimanual actions performed by an actor, from a lateral perspective (see Fig. 2-B1). Subsequently, the patient will be asked to imitate the actions presented for at least three consecutive times, within a time window of 3 min., using the same objects observed in the video, in a virtual scenario (VR), through the Khymeia VRRS system. During the execution of all exercises, the patient will wear also kinematic sensors for three-dimensional tracking of the performed movement, aimed to control objects in the virtual scenario. The treatment will include a total of 52 exercises, arranged as simple movements and complex sequences, either unimanual or bimanual, of increasing complexity. Examples of the proposed exercises are reported in Additional file 2. The protocol will include, for each week of training, a set of exercises subdivided in two parts, the first to be performed for two days, and the remaining to be performed in the remaining two days. For each exercise, the therapist will set the facilitation level, adjusting the sensitivity of kinematic sensors (levels range from 1 to 10) according to the patient's manual impairment. Facilitation level will be used particularly for those patients showing minimal residual hand ability, allowing them to perform the VR exercises. In more details, the exercises during the first week will include “no-gravity” movements (with no hand lifting) such as sliding to reach for a target located in different positions. The second and the third weeks will consists of “simple” and “complex” anti-gravity actions (requiring arm/hand lifting) respectively, either unimanual or bimanual. Furthermore, some bimanual functional exercises will be introduced, such as to put the toothbrushes in a glass, or to use knife and fork. The fourth week will consist of complex bimanual daily life actions, such as, for example, to wear sunglasses, or to draw a line with the ruler. Finally, during the fifth week, a set of more complex anti-gravity exercises will be proposed, including tasks of obstacles avoiding or following a path using a graspable floating pad device. Each session of AO + VR rehabilitation will take 30–45 min. to complete, including changing the setting between different exercises. The administration of personalized set of exercises will be adapted based on the patient hand motor performance at baseline, thus patients with minimal hand and arm ability will perform only no-gravity movements and simple anti-gravity actions, while patients with discrete hand ability will also perform the advanced exercises. Despite this type of adjustment of the treatment all the recruited patients will receive an equal number of treatment sessions, thus the final dose of the treatment will be balanced between the experimental and the control group.

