
#### *Control treatment (CO* + *VR)*

Participants randomly assigned to the control group will receive an equal number of rehabilitation sessions, as the experimental group. Differently from the latter, patients of the control group will be required to observe videos depicting naturalistic scenes (Fig. 2-B2), without motor contents, for 1.5 min. Then, they will receive a motor training in the VR environment, performing the same type of exercises included in the above-described experimental treatment, prompted by the verbal instructions of an expert therapist. Thus, the general setting for carrying out the rehabilitation sessions will be identical to that of the experimental group, except for the fact that the control group will not be involved in action observation before preforming the exercises. Thus, the control treatment is not based on action imitation, but on purely motor execution.

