### Concomitant care

Participants will continue to take medications for other conditions and rehabilitation treatments as usual care.

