#### Blinding

Participants and their caregivers will be informed about the study aims and procedures, but they will be blinded to group allocation. In the case the patient asks for the presence of the caregiver, she/he will be seated near the participant but out of her/his view, without interfering during the treatment session. The OT/PT performing the intervention will not be blinded to the group allocation. Outcome assessments will be administered and scored by a member of the staff blinded to group allocation.

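### Randomisation is stratified by hand use but not by centre, so the balance of arms within the two centres is left to chance; adding centre now is a cheap improvement

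*Protocol article*

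**What the plan says.** The Participants section states that "The multicentric study will take place in two clinical centers", and the Recruitment section names the same two as the places from which patients are invited.

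Treatment is given in person. Under Setting for VR rehabilitation, "A trained occupational therapist (OT) or a physiotherapist (PT) will assist the participants". In the experimental treatment, "the therapist will set the facilitation level, adjusting the sensitivity of kinematic sensors". In the control treatment the exercises are "prompted by the verbal instructions of an expert therapist". The Blinding section adds that "The OT/PT performing the intervention will not be blinded to the group allocation". Other rehabilitation goes on alongside: "Participants will continue to take medications for other conditions and rehabilitation treatments as usual care" (Concomitant care).

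The Randomization section gives 1:1 allocation from a computer-generated schedule, in permuted blocks of random and undisclosed size, "stratified by clinical level of the hand use (minimal vs. discrete". No other stratification factor is named, and separate lists per centre are not mentioned.

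The section on analysis of primary and secondary outcomes gives an independent-samples t-test (Mann-Whitney if normality fails), a group-by-time repeated measures ANOVA, and a linear mixed model for missing data and for the secondary endpoints. Centre appears in none of them. Study Status records that recruitment had not begun at submission.

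**The concern.** Read plainly, the blocks run within two hand-use strata that both centres share. Such blocks balance the arms for hand use, but a block can be filled by patients from either centre, so nothing holds the arms level within a centre.

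Centre is a plausible source of variation in the Box and Block Test (BBT) here. Therapists instruct patients and set the difficulty of each exercise, and the usual-care rehabilitation that continues is whatever patients otherwise receive. If the centres do differ, an uneven spread of arms moves this one trial's estimate by the imbalance times the centre difference. It also gives readers a reason to doubt the result. The list can be changed before the first patient is randomised and not afterwards.

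**Working it through.** **1. The plan's own figure.** Inputs from Sample size: difference 7, SD 11.3, power 80%, drop-out 10%. The two-sided 5% level comes from Statistical analyses.
- Normal approximation: n = 2 × (1.96 + 0.84)² × 11.3² / 7² = 40.9, so 41 per arm; 41/0.9 = 45.6, so 46.
- t-based: 41.9, so 42 per arm; 42/0.9 = 46.7, so 47.

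The stated 47 per group (N = 94) is reproduced. The sample size is not in question.

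**2. How uneven the centres can become.** Assumed, because the article does not give them: block sizes 2, 4 or 6; half the patients in each hand-use stratum; centre unrelated to hand use; the larger centre holding 50% to 80% of patients.

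As a rough check, if p is one centre's share, the between-arm difference in that share has SD of about √[p(1 − p) × 4/94]. This is √(0.25 × 4/94) = 0.103 at 50:50 and √(0.16 × 4/94) = 0.083 at 80:20. Simulated trials of 94 patients give SDs of 0.104 and 0.083, and these frequencies:

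| Stratified by | Centre split | Differ by ≥ 10 points | Differ by ≥ 15 points | 95th percentile of overall arm-size difference |
|---|---|---|---|---|
| Hand use only | 50:50 | about 35% | about 13% | 2 patients |
| Hand use only | 80:20 | about 23% | about 6% | 2 patients |
| Hand use and centre | 50:50 | none seen | none seen | 4 patients |
| Hand use and centre | 80:20 | none seen | none seen | 4 patients |

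Differences of 20 points or more are uncommon under the present scheme, at about 1 to 5% of trials. Using blocks of 4 or 6 hardly changes the picture: 22% at 80:20 and 36% at 50:50 for 10 points or more.

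**3. What that does to the estimate.** Shift = imbalance in centre share × centre difference in BBT. The documents give no centre difference, so two assumed values are shown: 2 blocks, and half the stated SD (0.5 × 11.3 = 5.65 blocks).

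| Imbalance | 2-block centre difference | 5.65-block centre difference |
|---|---|---|
| 10 points | 0.10 × 2 = 0.20 (3% of 7) | 0.10 × 5.65 = 0.57 (8% of 7) |
| 15 points | 0.15 × 2 = 0.30 (4% of 7) | 0.15 × 5.65 = 0.85 (12% of 7) |

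The standard error of the treatment difference with 47 per arm is 11.3 × √(2/47) = 2.33 blocks. The largest shift in the table is 0.85/2.33 = 0.36 of a standard error.

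**4. Share of variance at stake.** With equal centres that differ by half an SD, centre accounts for 0.25 × 0.5² = 0.0625, about 6% of total variance. The gain in precision is real but small.

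**The case against.** Stratifying on a prognostic hand-use factor is a valid choice, and leaving centre out is neither an error nor a contradiction. Several points on that side stand.

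- **No bias.** A reader might infer that a centre effect would pass for a treatment effect. Imbalance under proper randomisation is chance imbalance. If 11.3 is the total SD, it already contains between-centre variation, so the t-test's standard error and 5% error rate allow for it.
- **Unknown size.** No passage says that the centres differ in therapist skill or usual care. The VR system, the type of exercises and the number of sessions are common to both arms.
- **Assessors.** A reader might suppose that each centre has its own blinded assessor. The article says only that a staff member or investigator blinded to allocation does the assessment.
- **Therapists.** Stratifying by centre does not balance therapists within a centre. The article gives neither their number nor a rule for assigning them.
- **Consistency across centres.** It is tempting to say that a lopsided split prevents this from being judged. In a centre with 20% of patients (about 19), the standard error of its own effect is 11.3 × √(1/9 + 1/10) = 5.19 at 9:10 and 11.3 × √(1/13 + 1/6) = 5.58 at 13:6. The 95% half-widths are 10.2 and 10.9 blocks against a target of 7. Centre size is the obstacle, and stratification would not remove it.
- **Analysis.** Covariates may be set in an analysis plan that is not shown, and adjusting for centre there would deal with much of the imbalance.

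Two replies remain. The stratification factor is stated, so centre's absence from it is part of the plan as written and not merely condensed detail. If separate lists per centre are intended, the text needs only to say so. And an analysis plan can adjust for centre but cannot change how patients were allocated.

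**Conclusion.** The point holds as a cheap improvement to a stated allocation rule. With hand use as the only stratum, a centre-share difference of 10 points or more between arms would occur in roughly a quarter to a third of such trials, and of 15 points or more in about 6 to 13%. The resulting shift is 0.2 to 0.85 blocks, or 3 to 12% of the 7-point target. The consequence is some loss of precision and credibility, not bias or an inflated error rate.

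The frequencies rest on assumed block sizes, an assumed 50:50 hand-use split and centre shares from 50:50 to 80:20. The shift rests on an assumed centre difference of 2 to 5.65 blocks. The documents do not support taking the point further, to differing local assessors, to balance of therapists within a centre, or to a test of consistency across centres.

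**What to change.** Before the first patient is randomised, generate the schedule by centre and hand use (2 × 2 = 4 strata), keeping permuted blocks of random, undisclosed size, and state this in the Randomization section.

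Include centre and hand use as fixed effects in the primary analysis and in the linear mixed models. In practice the unadjusted t-test becomes a linear model with group, centre and hand use. Without these terms, balancing on a prognostic factor leaves the unadjusted test slightly conservative; with them, the standard errors reflect the stratification.

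The cost is one more factor in a computer-generated list, with no extra patients, visits or staff; N stays at 94. There are two modest downsides. The 95th percentile of the overall arm-size difference rises from 2 to 4 patients. Block ends also become slightly easier for unblinded local staff to guess, since they see every allocation in their own strata; random undisclosed block sizes limit this risk but do not remove it.
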